## Abstract

**Background:**

Most smokers start smoking during their early adolescence under the impression that smoking entails positive attributes. Given the addictive nature of cigarettes, however, many of them might end up as long-term smokers and suffering from tobacco-related diseases. To prevent tobacco use among adolescents, the large international medical students’ network Education Against Tobacco (EAT) educates more than 40,000 secondary school students per year in the classroom setting, using evidence-based self-developed apps and strategies.

**Objective:**

This study aimed to evaluate the long-term effectiveness of the school-based EAT intervention in reducing smoking prevalence among seventh-grade students in Germany. Additionally, we aimed to improve the intervention by drawing conclusions from our process evaluation.

**Methods:**

We conduct a cluster-randomized controlled trial with measurements at baseline and 9, 16, and 24 months postintervention via paper-and-pencil questionnaires administered by teachers. The study groups consist of randomized schools receiving the 2016 EAT curriculum and control schools with comparable baseline data (no intervention). The primary outcome is the difference of change in smoking prevalence between the intervention and control groups at the 24-month follow-up. Secondary outcomes are between-group differences of changes in smoking-related attitudes and the number of new smokers, quitters, and never-smokers.

**Results:**

A total of 11,268 students of both sexes, with an average age of 12.32 years, in seventh grade of 144 secondary schools in Germany were included at baseline. The prevalence of cigarette smoking in our sample was 2.6%. The process evaluation surveys were filled out by 324 medical student volunteers, 63 medical student supervisors, 4896 students, and 141 teachers.

**Conclusions:**

The EAT cluster randomized trial is the largest school-based tobacco-prevention study in Germany conducted to date. Its results will provide important insights with regards to the effectiveness of medical student–delivered smoking prevention programs at school.

**International Registered Report Identifier (IRRID):**

DERR1-10.2196/13508

## Introduction

### Background

Most smokers start smoking during their early adolescence with the idea that smoking entails positive attributes; at this age, the health risks of smoking such as those related to vascular disease, lung cancer, and chronic pulmonary disease are too far in the future for them to fathom. Given the addictive nature of cigarettes, however, many smokers might end up as long-term smokers and suffering from severe and potentially deadly tobacco-related diseases [1].

Despite the fact that effectiveness of inpatient smoking cessation was demonstrated in major trials [2] and that these measures were implemented in the guidelines of almost all medical specialties [3], research has shown that physicians in Germany lack both motivation (eg, role incongruence as a major barrier [4,5]) and education to deliver such measures [4-7], especially before the onset of chronic disease [5]. The issue of undertreatment of tobacco use by physicians is known on a global scale [8,9]. It is estimated that global tobacco-attributable mortality will double from 5 million (2010) to 10 million per year in a few decades [1].

Education Against Tobacco (EAT) is a multinational network of medical students that aims to provide science-based tobacco prevention to a large number of adolescents and to thereby sensitize prospective physicians toward the importance of inpatient smoking cessation [10-12]. The network currently involves about 80 medical schools in 12 countries, with 3500 medical students educating more than 40,000 secondary school students in the classroom setting per year using and optimizing self-developed apps and strategies (Multimedia Appendix 1) [13-15]. The two free science-based quit apps of EAT (“Smokerface” and “Smokerstop”) were downloaded more than 400,000 times and translated in the most spoken languages worldwide (Multimedia Appendix 1) [14,15].

The 2018 KiGGS report by the German Robert Koch Institute revealed that 9.3% of German boys and 8.9% of German girls aged 14-17 years smoke cigarettes at least once a week [16]. In spite of the decline in adolescent smoking over the last two decades, prevalence in Germany is among the highest in Europe, and strong socioeconomic differences in smoking habits exist [17-19].

### Current Knowledge on School-Based Tobacco Prevention

Most school-based smoking prevention–related curricula are ineffective, and the evaluation of new curricula is warranted [20]. A recently published evaluation of a short student and student-parent smoking prevention program in Germany did not show significant effectiveness among seventh-grade students (7.6% and 7% prevalence in intervention groups, respectively, vs 10.1% in the control group) at the 24-month follow-up. However, this might have been due to a very low sample size: Only 47 schools were randomized because of an underestimated intracluster correlation coefficient [21,22]. The largest tobacco-prevention program for secondary schools in Germany—the smoke-free class competition—has demonstrated limited effectiveness in making students quit and increasing knowledge among students and was not able to prevent smoking onset [23-25].

Physician-based programs relying on fear-inducing statements show no overall long-term effectiveness in reducing the prevalence of smoking [26-29]. Limited new evidence suggest that asking questions about health consequences rather than making statements might be more effective to at least motivate current smokers to quit [30].

A physician-based multimodal program in Berlin, where students attended a 2-h interactive presentation of smoking-related health consequences, evaluated in a quasi-experimental study suggested significant short-term effects of preventing smoking onset, which might be a promising alternative to the traditional fear approaches of physician-based programs [31]. Outside of schools, a systematic review on inpatient physician-based smoking prevention and cessation for adolescents revealed that behavioral interventions show overall effectiveness in primary care [32].

### Previous Research on Education Against Tobacco

The effectiveness of an earlier version of the EAT curriculum on reducing smoking prevalence among adolescents has only been investigated with a quasi-experimental design (n=1474) with potential sources of bias [10,11]. However, the study showed a significant association of the intervention with lower smoking prevalence among secondary school students in Germany at 6 months of follow-up by motivating them to quit. After this first evaluation, the curriculum was optimized for students with a lower educational level by using cognitive interviewing, as the intervention was found to be less effective in this subgroup. The curriculum received more age-appropriate content, was optimized to be more interactive and gain framed [33], and was equipped with app-based strategies [10,14].

### Education Against Tobacco Apps: “Smokerstop” and “Smokerface”

Photoaging desktop programs in which an image is altered to predict future appearance were effective in motivating girls aged 14-18 years to quit smoking and increased the quit rate in young adults aged 18-30 years of both genders by 21% [34,35]. We took advantage of the broad availability of smartphones and adolescents' interest in appearance to create a free 3D-photoaging smartphone app “Smokerface” [15], which animates the users’ selfies and reacts to touch (Multimedia Appendix 2). It is downloaded 200 times per day, and the current version of the app has a rating of 4.2/5 in the Google Play Store (Google LLC, Mountain View, CA) and 4.5/5 in the Apple AppStore (Apple Inc, Cupertino, CA).

Our second free quit app is called “Smokerstop” and was developed based on theory [36] and evidence [37] from conventional smoking-cessation programs. The underlying concept is the PRIME Theory, which has been described in great detail elsewhere [38,39]. Our app takes into account recent research on adequate coping strategies for craving [40,41]. About 1000 smokers per day use this app to support their quit attempt, and it has an average rating of 4.5/5 in the AppStore and Play Store. Smokerface motivates people to remain smoke free or to make a quit attempt and is likely to help with continuous abstinence [14]; in contrast, Smokerstop supports quitters who are already prepared to set a quit date. Both apps are a part of our school-based intervention.

We designed this randomized trial to answer the following questions:

Does medical student–delivered prevention by EAT show effectiveness in reducing smoking prevalence in secondary schools?Which subgroups (ie, gender, education level, and cultural background) benefit most from this intervention?Is this low-cost campaign effective in convincing students to use the apps?Which students are more likely to use an app revealing the photoaging effects of smoking?

## Methods

### Ethics Approval

The study protocol was approved by the ethics committee of the University of Giessen and the ministries of cultural affairs of the five participating federal states. Written informed consent was obtained by the responsible teachers from both the participants themselves and their parents. All participant information will be stored in locked file cabinets in areas with limited access. Participants’ personal information will not be released outside of the study without written permission of the participants. Study results will be disseminated at national and international conferences, in peer-reviewed journals, on our websites, and throughout the multinational EAT network.

### Trial Design

A randomized controlled multicentered trial with two parallel groups is underway (ClinicalTrials.gov: NCT02697409). A total of 13 German EAT groups are participating, each functioning as a study center. The primary outcome is the between-group difference in smoking prevalence from baseline to follow-up. Randomization was externally and centrally performed via a computer on a school level with a 1:1 allocation.

A total of 144 secondary schools in five federal states of Germany participated in the baseline survey in the first half of the school year (September 2016 to April 2017, depending on the federal state) prior to randomization. The randomization of schools based on the baseline data was performed from November 2016 through May 2017 by the Coordination Center for Clinical Studies Marburg (KKS Marburg) as a blocked randomization combined with stratified randomization by study center and smoking prevalence, in order to ensure a balance of participant characteristics in each group. Immediately after randomization, schools were informed of their group allocation (intervention or control) and appointments were made for the implementation of the EAT curriculum in the intervention group. To assess the quality of the intervention, we implemented a process evaluation including four points of view: medical student volunteers and training supervisors after training via the EAT curriculum as well as teachers and students within 24 hours postintervention. The first follow-up survey was conducted 9 months after the intervention. The second follow-up was conducted at 16 months (April 2018 to February 2019), and the third follow-up will be conducted at 2 years (December 2018 to October 2019). In order to assure comparability between the two groups, we calculated the average number of days between randomization and intervention in each study center for the intervention group and added these numbers to the randomization date of the schools in the control group when assessing the dates for the follow-up surveys.

### Intervention

#### Before the Visit

We sent letters to teachers to prepare them for our visit. Parents received letters to motivate them to quit smoking via the Smokerface App and to attempt to quit with the Smokerstop App [42] in case they are smokers themselves while informing them on how to best ensure that their children do not take up the behavior, summing up recent pertinent scientific publications in layman’s terms [43-46]. The students were advised to prepare for our intervention by downloading the Smokerface App on their smartphone [14]. The medical student volunteers were trained in the 2016 EAT curriculum by experienced supervisors in all cases and by long-term group leaders of the EAT network of medical students, via a standardized preparation curriculum.

#### In Schools

In the first part of the intervention, lasting for about 45 minutes, all participating classes of Grade 7 will gather in a large room under the supervision of at least two medical students. For the first 30 minutes, students will be interactively involved in a PowerPoint (Microsoft Corp, Redmond, WA) presentation that discusses how smoking affects the performance of German soccer players, addiction, costs, relaxation/happiness, and strategies of the tobacco industry and are interviewed about how they would advertise cigarettes to the rest of their grade. In the last 15 minutes, our photoaging app is implemented into the school setting via a self-developed strategy called “mirroring”: The students’ altered 3D self-portraits on mobile phones or tablets are “mirrored” via a projector in front of their whole grade [14]. In a recently published pilot study, we were able to demonstrate that this type of implementation influences multiple predictors of smoking in accordance with the theory of planned behavior [14,47].

The second part of the intervention, lasting about 90 minutes, is designed to be as interactive as possible: The students are sent to their classrooms where they are split into three groups with three medical students per room. There, they rotate to four different stations in the classroom, which discuss age-appropriate information, ask about their own experiences, and have them conduct their own experiments.

### Different Tobacco Products and Extraction of Substances of Tobacco Smoke

In the first part, different products (including electronic cigarettes [e-cigarettes], waterpipe, and cigarettes) are displayed and explained, and their harmfulness is discussed in a gain-framed manner.

In the second part, the students will observe an experiment using a napkin, a prepared plastic bottle filled with water, and a cigarette. The cigarette is fixated at the bottleneck via a rubber plug and burned, while the water is drained through a hole in the bottom of the bottle to create a vacuum. After the vacuum makes the smoke flow into the bottle, the cigarette is removed, and the napkin is put around the bottleneck. The smoke then gets blown out of the bottle through the napkin, which demonstrates the tar in the smoke by the discoloration of the napkin. When proper ventilation is not ensured, the medical students and school students will conduct the experiment outside to avoid unnecessary exposure to second-hand smoke.

### Attractiveness and Mechanisms Related to the Face

In the first part, pictures of monozygotic smoking/nonsmoking twins are displayed, which are extracted from the publication of Okada et al [48]. The students are asked which twin is the smoker and what differences they note between the twins.

In the second part, Galaxy Tab A tablets (Samsung Electronics Inc, Seoul, Korea) are used to show each student the effects of smoking/nonsmoking on their own faces by the help of the photoaging app Smokerface that we described and piloted in great detail elsewhere [14,15]. As such, the students’ faces are captured via a selfie and photoaged into a 1- to 15-year older version of themselves (normal aging vs normal aging + smoking) with animated touch effects (Figures 1-4,Multimedia Appendix 1). This intervention has been shown to influence numerous predictors of smoking in students of this age group in accordance with the theory of planned behavior and as demonstrated in our recent paper [14].

**Figure 1 figure1:**
[figure not shown]
Female poster at baseline.

**Figure 2 figure2:**
[figure not shown]
Male poster at baseline.

**Figure 3 figure3:**
[figure not shown]
Female version of post-15 year Smokerface poster at 1 year postintervention.

**Figure 4 figure4:**
[figure not shown]
Male version of post-15 year Smokerface poster at 1 year postintervention.

### Performance Benefits of Nonsmoking

Performance benefits of nonsmoking (physical performance, stress, and common colds) and understanding the *mechanisms* of *how* tobacco smoking affects the body with age-appropriate examples (eg, occluded vessels lead to loss of connective tissue in women’s breasts, which is equivalent to less volume/tightness; impotence in both men and women; pale skin; and mechanisms of acne); this is explained via pencil and paper drafts and interactive questions. In addition, obesity [49,50], lung growth [51], and body growth impairment in adolescent smokers are discussed using a body model, paper-pencil sketches, and growth curves [50].

### Personal Experiences: How Can I Stay Away From Smoking?

The aim of this station is to discuss the students’ own experiences with tobacco and how they reacted to peer pressure in the past. The group’s knowledge/experience is shared and discussed in a team setting where the medical students take the role of older friends to complement the students’ experiences with their own experiences in order to increase students’ perceived self-efficacy, which is the most important predictor of future smoking according to the theory of planned behavior [47]. It has been shown to predict both the intention to smoke and actual smoking behavior in a meta-analysis [52].

At the end of the classroom seminar, we will ask for the students’ final judgments on smoking to create positive peer pressure and influence students’ subjective norm in accordance with the theory of planned behavior [47]. Health consequences are not discussed in great detail, as fear approaches were proven to be ineffective and information on smoking-related diseases can be found on every cigarette pack [25]. As a final exercise, all students breathe through a straw after having physically exercised in the classroom together to learn how lung impairment due to smoking feels with exercising. The medical students hang up the first two self-developed posters of the Smokerface App poster campaign, which has been described in great detail elsewhere [53].

#### After the Visit

One-year postintervention, the Smokerface App posters showing a 1-year difference of smoking are replaced with a version showing a 15-year difference.

According to a recent Cochrane review [20], smoking parents should be involved and encouraged to stop smoking, as adolescents are twice as likely to start smoking if their parents do [42]. However, increased perceived parental control increases the likelihood of adolescents to choose smoking friends and needs to be avoided [43]. To further increase the use of the apps and to guide smoking cessation among parents within the intervention group, the intervention posters will be complemented by letters to the students and parents (delivered along with the questionnaires at the 9-, 16-, and 24-month follow-ups).

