### Outcomes

The primary outcome is the between-group difference of the change in smoking prevalence from baseline to the 24-month follow-up. Secondary outcomes are between-group differences in change in smoking-related attitudes in accordance with the theory of planned behavior and the number of new smokers, quitters, and never-smokers after 24 months. For all outcomes, the number needed to treat will be calculated. Considering the short nature of the intervention, we predefined a number needed to treat below 50 as clinically relevant. Students are defined as smokers if they report having used cigarettes, at least one day in the 30 days preceding the survey, in accordance with the established National Youth Tobacco Survey definition [58]. Students who report not having smoked cigarettes in the past 30 days were defined as nonsmokers. All participants who report having smoked more than a puff in the past (beyond the past 30 days) were defined as ex-smokers.

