### Baseline Characteristics

Our baseline survey includes the major predictors of adolescent smoking, as described in the literature [56,57]. The distributions of relevant characteristics over the two groups are balanced, indicating successful randomization. For example, the students in the intervention and control groups are similar with regard to the current smoking prevalence (2.4% and 2.7%, respectively), never-smoking prevalence (85.0% and 84.0%, respectively), and the proportion of those having at least one smoking parent (38.6% and 38.4%, respectively).This large study is conducted in five German federal states. Our definitions for the smoking status of the various monitored tobacco products stem from the National Youth Tobacco Survey by the Center for Disease Control (Atlanta, United States) [57]. Teachers are used as data collectors and were handed out a modified protocol, as used in the Hutchinson Smoking Prevention Project to ensure international comparability.

This is also the first national study to show that current e-cigarette prevalence is higher than cigarette smoking prevalence in Grade 7 students from secondary schools (2.6% use cigarettes and 4.7% use e-cigarettes). More than a quarter of these (1.3% of the total sample) currently use both products at the same time. The epidemiologic data presented here are therefore also valuable, considering that the most cited and most recent surveys in Germany were conducted via telephone interviews, a method showing poor consistency with biochemical validation in our age group [17,63]. We are not using biochemical validation in our study because it would have to take place in the school setting with previous notice on the day the paper questionnaires are given out. This would compromise the comparability of data obtained on that day, since students may answer according to social desirability.

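### Intervention-arm letters are scheduled with the follow-up questionnaires, which allows an avoidable one-arm reporting cue when the self-reported primary outcome is measured

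*Protocol article*

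**What the plan says.** All references are to the protocol article.

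- **Who gets letters, and why.** After the Visit gives the purpose as "To further increase the use of the apps and to guide smoking cessation among parents within the intervention group". The means are "letters to the students and parents (delivered along with the questionnaires at the 9-, 16-, and 24-month follow-ups".
- **Control arm.** The Abstract (Methods) describes "control schools with comparable baseline data (no intervention".
- **Primary outcome.** Outcomes states: "The primary outcome is the between-group difference of the change in smoking prevalence from baseline to the 24-month follow-up". Smoking status is self-reported: "Students are defined as smokers if they report having used cigarettes, at least one day in the 30 days preceding the survey".
- **Mode of measurement.** Data are collected "via paper-and-pencil questionnaires administered by teachers" (Abstract, Methods). Trial Design says that schools were told their allocation straight after randomization.
- **No objective check.** The Discussion (Baseline Characteristics) says "We are not using biochemical validation in our study". The reason given is that notice of testing on questionnaire day would harm the comparability of that day's data, because "students may answer according to social desirability".

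**The concern.** The contact at which the primary outcome is measured carries a programme message in one arm only. The outcome is a retrospective self-report with no biochemical check, collected in schools that know their allocation. If the letter reaches students before they answer, some intervention-arm smokers may be less willing to admit smoking.

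The protocol accepts that a survey-day influence can shift answers, since that is its reason for rejecting biochemical validation. Testing would at least have applied to both arms, whereas the letters go to one.

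Under-reporting in one arm would look like programme benefit. Change from baseline would not cancel it, because the baseline survey came before randomization and so carried no arm-specific letter. The hierarchical models and the multiple imputation described under Analysis would not remove it either, since they take the recorded answers as true. The self-reported attitudes among the secondary outcomes are exposed in the same way.

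**Working it through.** **1. The plan's own figure.** Sample Size Calculation gives 5645 to 15,715 participants for a 3-point difference (two-sided alpha 5%, power 70%, ICC 0.033, cluster size 100, dropout 30%).

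- Design effect = 1 + (100 − 1) × 0.033 = 4.267.
- The pooled two-proportion formula without continuity correction gives 463 per arm for 2% vs 5% and 1289 per arm for 9% vs 12%.
- 2 × 463 × 4.267 / 0.70 = 5645, and 2 × 1289 × 4.267 / 0.70 = 15,715.

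Both figures reproduce. The sample size is not in dispute and serves here only as a yardstick.

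**2. Yardsticks.** The planned effect is 3 points. Outcomes predefines a number needed to treat below 50 as clinically relevant; 1/50 = 2 points.

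**3. What each letter can affect at 24 months.** The outcome looks back 30 days. A letter arriving with the 24-month questionnaire comes after that window, so it cannot change the behaviour being measured. Seen before answering, it can change only the report; seen after collection, it changes neither. The 9- and 16-month letters come early enough to affect behaviour by 24 months and are ordinary parts of the intervention.

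**4. Size under assumptions.** Suppose there is no true effect, the control prevalence at 24 months is p, and a share u of intervention-arm smokers deny smoking because of the cue. Then

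spurious difference = p − p(1 − u) = p × u.

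The values of u are assumptions; the document gives no figure for them. For p, 5% and 12% are the higher rates in the two sample-size scenarios, taken here as the control rates. The value 10% is close to the 10.1% control prevalence at 24 months in the earlier German trial cited under Current Knowledge on School-Based Tobacco Prevention.

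| p | u = 10% | u = 20% | u = 30% | u needed for 2 points | u needed for 3 points |
|---|---|---|---|---|---|
| 5% | 0.5 | 1.0 | 1.5 | 40% | 60% |
| 10% | 1.0 | 2.0 | 3.0 | 20% | 30% |
| 12% | 1.2 | 2.4 | 3.6 | 17% | 25% |

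(Columns 2 to 4 are percentage points.)

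**5. Chance of a falsely significant benefit.** With 11,286 students, 144 schools and 30% dropout:

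- per arm: 11,286 × 0.70 / 2 ≈ 3950
- students per school: 11,286 × 0.70 / 144 ≈ 54.9
- design effect: 1 + 53.9 × 0.033 ≈ 2.78
- effective number per arm: 3950 / 2.78 ≈ 1422

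A normal approximation for two proportions, at u = 20% and no true effect, gives a significant result in favour of the programme with probability of about 25% at p = 5%, 46% at p = 10% and 54% at p = 12%. The nominal value in that direction is 2.5%. At u = 10% the probabilities are about 9%, 15% and 17%. This is a rough guide, since the planned main analysis is a hierarchical model.

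**The case against.** The strongest objection is that the order of events is not stated. A reader might infer that students answer with the letter already read, so that the primary outcome is in fact measured under priming. The wording in After the Visit does not support that: it can equally describe a shared shipment to the school, with letters handed out once questionnaires are in. Data Collection says that teachers work from a modified protocol taken from an earlier prevention project, and that instruction, which is not shown, may already settle the order. This stands, and it limits the point to a risk. It does not dispose of it, because the article itself fixes joint delivery at all three follow-ups and nowhere says that questionnaires are collected first or that control schools get a neutral letter.

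Other objections stand in part:

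- The letter text is not shown. Only its aims are known: app use and parental cessation. That controls receive no letter is inferred from their receiving no intervention.
- A letter promoting an app is not equivalent to notice of a biochemical test, which tells students that their answers will be checked. The comparison shows only that the protocol takes survey-day influences seriously.
- Students' assurances may reduce the effect. At baseline 94.0% said anonymity had been explained and 76.6% recalled the confidentiality explanation (Quality of Data Collection).
- The classroom programme and the posters can also produce differential reporting. Some of this is unavoidable in an unblinded school trial, and only the letter's increment is at issue here.
- At 5% prevalence, 40% extra denial would be needed to reach even the 2-point threshold, so the threat is much weaker at the low end of the planned range.

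**Conclusion.** The point holds as an avoidable risk of bias. The stated delivery timing allows an arm-specific cue at the measurement of an unvalidated self-reported primary outcome, and any resulting bias would favour the programme. The documents do not show that such bias occurs, and its size is unknown.

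Under assumed extra denial of 10 to 30%, the spurious difference runs from 0.5 to 1.5 points at 5% control prevalence and from 1.2 to 3.6 points at 12%. At 10% prevalence, 20% denial would equal the 2-point relevance threshold and 30% would equal the planned effect. These figures assume no true effect, charge all the denial to the letter, and require that the letter be seen before the questionnaire is completed.

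The case for acting rests less on these magnitudes than on the 24-month letter having no possible benefit for the endpoint measured at that wave.

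**What to change.** Change the delivery timing in After the Visit, and match it in the teacher instruction:

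1. In every school, questionnaires are completed, collected and sealed before any letter is distributed.
2. The 24-month letter goes out only after that school's 24-month survey is closed.
3. For waves already collected, establish whether letters came before, with or after the questionnaire, and report this as a limitation.

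Trial Design places the third follow-up in the future (December 2018 to October 2019), so the primary time point can still be protected in schools not yet surveyed. The cost is one instruction line and a separate envelope or later mailing. The content of the intervention does not change. Differential reporting due to the programme itself and the posters would remain and should be acknowledged when the result is interpreted.
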